## Abstract

**Introduction:**

Low back pain (LBP) is a prevalent and costly condition. The majority of patients experiencing LBP are managed in primary care, where first-line care recommendations consist of advice to self-manage and remain active. Internet interventions present a potential means of providing patients with tailored self-management advice and evidence-based support for increasing physical activity.

**Methods/analysis:**

This protocol describes a single-blind, randomised controlled feasibility trial of an internet intervention developed to support the self-management of LBP in primary care. Patients are being randomised to 1 of 3 groups receiving either usual primary care, usual primary care with the addition of an internet intervention or an internet intervention with physiotherapist telephone support. Patients are followed up at 3 months. Primary outcomes are the feasibility of (1) the trial design/methods, (2) the delivery of the internet intervention and (3) the provision of telephone support by physiotherapists. Secondary outcomes will include exploratory analysis of estimates and variation in clinical outcomes of pain and disability, in order to inform a future main trial.

**Ethics/dissemination:**

This feasibility trial has undergone ethical scrutiny and been approved by the National Health Service (NHS) Research Ethics Committee, REC Reference 13/SC/0202. The feasibility findings will be disseminated to the research community through presentations at conferences and publication in peer review journals. Broader dissemination will come following a definitive trial.

**Trial registration number:**

ISRCTN 31034004.

Strengths and limitations of this studyThis protocol describes a randomised controlled feasibility trial of a novel internet intervention for primary care patients with low back pain, provided in addition to usual primary care.This study will explore adding physiotherapist telephone support to the internet intervention.Using the internet as a delivery mode for the intervention may exclude some primary care patients where access to the internet is limited.

## Introduction

Low back pain (LBP) is common; lifetime prevalence estimates range from 65% to 84%.^1^
^2^ Each year approximately 6–9% of the UK population will visit their general practitioner (GP) with LBP, at a cost of around 251 million pounds to the National Health Service (NHS) per annum.^3^
^4^ Although acute LBP is often reported as a relatively brief, self-limiting condition,^5^ Henschke *et al*^6^ showed that around a third of patients presenting with acute symptoms had not recovered at 12 months. In studies including all primary care consulters with LBP, up to 52% of patients had poor clinical outcome at 6 months,^7^ and Dunn *et al*^8^ showed LBP trajectories for primary care consulters appear to remain stable with 69% of patients continuing to report mild to persistently severe pain at 7-year follow-up. Where LBP becomes recurrent or persistent (estimates range widely from 2% to 56%^9^
^10^), patients are at risk of becoming deconditioned, depressed and immobile, reducing their ability to work and leading to extensive healthcare and societal costs. With regard to disease burden, Hoy *et al*^11^ recently demonstrated that LBP caused more global disability than any other condition.

Promoting effective self-management is a key strategy in the care of patients with LBP.^12^
^13^ Definitions of self-management vary; however, central components include monitoring of the health condition and effecting the cognitive, behavioural and emotional responses necessary to maintain quality of life, and where possible, reduce symptom-related disability.^14^ Encouraging physical activity and exercise is recommended within LBP treatment guidelines,^13^
^15^ and physical activity is a core component of self-management programmes.^12^ Alongside physical activity, targeting psychological processes such as self-efficacy,^16^ pain perceptions, expectations and fear-avoidance beliefs may also be important in interventions for LBP.^17^ For those needing support to regain their self-efficacy, overcome common concerns and regain active lifestyles, GP referral to physiotherapy is common, with UK estimates suggesting 20% are referred to a physiotherapist in the UK.^18^ Recent research suggests caution regarding advice on the pharmacological management of symptoms;^19^ concerns have been raised about the effectiveness of paracetamol^20^ and oral non-steroidal anti-inflammatory drugs (NSAIDs) may not be suitable for patients with contraindications, particularly prevalent in older adults.^13^ This recent research highlights the important role of non-pharmacological self-management in the care of patients with LBP.

The majority of patients with LBP will be seen by GPs in primary care.^21^ GPs’ consultations with patients are typically short, and after ruling out serious spinal pathology, GPs are unlikely to have the resources or training to deliver optimal evidence-based behavioural support. Interventions delivered over the internet may be well placed to complement time-constrained GPs in providing tailored information, advice and support for self-management.

Internet interventions are structured programmes that patients engage with by using computers or mobile devices (including tablets), over a set period of time. In addition to providing tailored educational information, they can support self-management by facilitating goal setting, self-monitoring and providing behavioural/symptom-related feedback. Along with heightened interactivity, internet interventions can provide audio and video material, broadening the scope for content beyond traditional paper-based media for delivering LBP-related education and advice.^22^ Internet interventions delivered with ‘live’ health professional support, which can be minimal, have been shown to be more effective than internet interventions delivered without support.^23^ However, this is not always the case^24^ and removal of health professional time may ensure these interventions can be offered more broadly and cost-effectively, potentially increasing access.

With all technology-mediated health innovations, it is essential to remain vigilant to how access limitations might exclude certain groups of society. Nonetheless, it is important to reflect on this in light of access to traditional services. For instance, household internet access in the UK is reported to have now reached 84%,^25^ and is expected to continue to grow. These increasing figures suggest that internet interventions may in fact become more accessible than many traditional face-to-face services, where patients’ access will be restricted by factors such as availability of transport, childcare and working hours.

Previous research on internet interventions for back pain has focused almost exclusively on chronic pain and psychological approaches to managing symptoms such as cognitive behavioural therapy (CBT).^26–29^ Although results are promising,^26–29^ sample sizes are small and control groups are commonly either waiting lists or no treatment conditions, thus it is unclear how internet interventions when added to usual primary care might compare to usual primary care alone. GPs see the full spectrum of patients with LBP from acute to chronic/persistent pain. There is a need to explore the utility of internet interventions that have been designed to be broadly applicable for a wide range of patients presenting with LBP. It is also necessary to examine the provision of health professional support for LBP interventions with wider scope. CBT therapists have often been used to provide support for internet interventions specifically for chronic pain.^26^ Physiotherapists are integral members of the LBP clinical pathway in the UK NHS, and are well placed to deliver first-line rehabilitation with specialist skills in assessment and re-enablement to promote active and healthy lifestyles. Thus, physiotherapists may be the most appropriate choice to provide support for a LBP internet intervention targeting primary care patients.^30^

### Aims and objectives

We aim to explore the feasibility of providing an internet intervention for patients with LBP in primary care, with and without physiotherapist telephone support (in addition to usual care), compared with usual care alone. The feasibility of physiotherapists delivering limited telephone support for the intervention will also be explored.

Our objectives are to determine: (1) the feasibility of the trial procedures, including: recruitment of general practices and patients; the appropriateness of screening procedure and the selected measures; patient retention and data completion rates. (2) The acceptability of the internet intervention in supporting patient's use of, and adherence to, the intervention as well as physical activity recommendations, and the experience of patients in the intervention groups (this will be explored qualitatively). (3) The feasibility of physiotherapist telephone support, including: ability to contact patients; physiotherapists’ adherence to protocol; duration and number of calls made to patients. These objectives should enable decisions about the feasibility of moving to a definitive trial in future, and identify areas where the trial design may need to be modified.

## Methodology

### Design and setting

A single-blind, single-centre randomised controlled trial with three parallel arms to explore the feasibility of an internet intervention for patients with LBP in primary care. The trial will be carried out in 10–15 UK general practices in the south of England.

### Participants

The following eligibility criteria will be applied:

*Inclusion*: Patients will: have current LBP (have experienced pain within the past 2 weeks); have access to the internet and an active email address; have had a prior LBP consultation at their general practice within the past 6 months for those invited directly from practice lists; be able to read/understand English without assistance.

*Exclusion*: Patients will be excluded if: they are under 18 years of age; have clinical indicators of potentially serious spinal pathology or systemic illness; they have taken part in the study to develop the internet intervention is being trialled.

### Identification, invitation, screening and recruitment

This trial is supported by the UK Clinical Research Network Division 5 who are facilitating the recruitment of primary care practices for the trial. Once recruited, GP practice staff identity patients via two methods:

(1) Patients who have consulted with LBP in the past 3 months are identified from practice computerised records of consultations. The timeframe of the search will be extended to 6 months if the number of patients identified is limited. Lists of patients identified by the search are being screened by a practice GP who will rule out patients based on aspects of the eligibility criteria that can be determined from patient notes. Practices then send out study packs to the patients deemed eligible at this stage. Study packs include an invitation letter from the GP, a patient information sheet and contact details of the research team should the patient be interested in taking part. This method of identification and invitation of eligible patients is expected to be the main method used by practices.

(2) Patients are opportunistically identified by GPs in clinics. GPs briefly mention the study to eligible patients in the consultation and provide the patients with a study pack.

Patients who respond to the research team are further screened by the study manager. The study manager contacts the patient by phone and confirms eligibility by asking if they have current back pain (currently in pain, or have experienced pain in the past 2 weeks). Patients are then asked if they are experiencing 1 or more of 12 symptoms indicative of serious spinal pathology or systemic illness. These questions were initially developed for telephone-based musculoskeletal triage, and modified for this trial by the clinicians in the research team. See table 1 below for details.

**Table 1 BMJOPEN2015009524TB1:** Screening questions relating to serious spinal pathology or systemic illness

High-level musculoskeletal safety questions			
I now need to ask you some very important questions			
1	Since this problem in your back started have you had a sudden, severe, worsening pain in the middle of your abdomen and upper back?	Yes	No
2	Do you have a new or recent problem in being able to pass urine?	Yes	No
3	Do you have a new or recent loss of control of your bladder and/or your bowels?	Yes	No
3a	Has your bladder been working properly? Can you tell when it is full? Have you felt that you want to ‘go’ all the time?	Yes	No
4	Do you have numbness or altered feeling or pins/needles around your back passage or genitals, for example, wiping after being at the toilet?	Yes	No
5	Since this problem in your back started have you had any heat, swelling or tenderness in your calf?	Yes	No
6	Since this problem in your back started have you been unable to put any weight at all through your legs?	Yes	No
7	Do you have constant pain that worsens at night?	Yes	No
8	Do you have a history of cancer?	Yes	No
9	Since this problem in your back started have you had any widespread or worsening weakness in your legs?	Yes	No
10	Did this episode of pain start following a fall, or get much worse and stay bad following a fall?	Yes	No
11	Do you have any chills or fevers or feel like you are running a temperature? (without other explanation)	Yes	No
12	Do you have trouble with your balance while walking?	Yes	No
12a	If ‘Yes’ above, has this changed during the current episode?	Yes	No

If a patient answers yes to one or more of these screening questions, the details are discussed with a senior clinician and where appropriate, referred back to their GP. If patients report that they are experiencing LBP, report no indicators of potential serious spinal pathology or systemic illness, and are interested in participating, they are emailed a link to the trial website. On this website, they provide online consent (patients have a chance to ask questions about the study in the screening phone call), complete online baseline measures and are automatically randomised to one of three intervention arms. If patients experience any technical difficulties during this online automated process, they receive telephone support from the study manager.

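### Screening item 3a combines three bladder questions of opposite direction in one Yes/No answer, while the escalation rule acts only on Yes

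*Protocol article*

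**What the plan says.** The section on identification, invitation, screening and recruitment (Protocol article) describes a telephone screen by the study manager. It introduces the questions as follows: "Patients are then asked if they are experiencing 1 or more of 12 symptoms indicative of serious spinal pathology or systemic illness". Table 1 lists them as items 1 to 12 plus sub-items 3a and 12a, each row with its own Yes/No pair.

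Item 3a holds three questions on one row: "Has your bladder been working properly? Can you tell when it is full", followed by "Have you felt that you want to ‘go’ all the time".

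The escalation rule stands directly after the table: "If a patient answers yes to one or more of these screening questions, the details are discussed with a senior clinician", with referral back to the GP where appropriate. It gives no exception or reverse scoring for 3a.

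The other sub-item, 12a, is expressly conditional: "If ‘Yes’ above, has this changed during the current episode". Item 3a has no such marker.

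The same section gives the trial link only to patients who report no sign of serious pathology. The Participants section excludes patients with such clinical indicators.

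**The concern.** A rule that acts on Yes works only if Yes is the worrying answer on every row. On 13 of the 14 rows it is. Item 3a is the exception: two of its three questions ask whether function is normal, and the third asks about a symptom. One answer cannot serve both directions.

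The screen is there for safety. If the rule is applied as printed, a patient whose bladder is not working properly and who cannot feel when it is full could answer No throughout 3a without triggering the clinician discussion. A patient with normal function would trigger it. Whatever is ticked, a later reader of the form cannot tell what the patient reported. No effect on the sample size, outcomes or analyses is at issue.

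**Working it through.** No figure in the article is in dispute, so there is nothing to reproduce. The check is one of logic.

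**Inputs, all from Table 1 and the rule after it**
- Rows: items 1 to 12 (12) + 3a + 12a = 14 Yes/No answers.
- Questions: 13 single-question rows + 3 in item 3a = 16.
- Item 3a: part 1 (working properly), No is the concern; part 2 (can tell when full), No is the concern; part 3 (wants to go all the time), Yes is the concern.
- Literal rule: escalate if any part is answered Yes.
- Rule by meaning: escalate if part 1 = No, or part 2 = No, or part 3 = Yes.

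**Reading A: 3a is a stand-alone item.** Three two-way answers give 2 × 2 × 2 = 8 patterns.

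| Parts 1/2/3 | Concerns | Literal rule | By meaning | Agree? |
|---|---|---|---|---|
| Yes/Yes/Yes | 1 | escalate | escalate | yes |
| Yes/Yes/No | 0 | escalate | do not | **no** |
| Yes/No/Yes | 2 | escalate | escalate | yes |
| Yes/No/No | 1 | escalate | escalate | yes |
| No/Yes/Yes | 2 | escalate | escalate | yes |
| No/Yes/No | 1 | escalate | escalate | yes |
| No/No/Yes | 3 | escalate | escalate | yes |
| No/No/No | 2 | do not | escalate | **no** |

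The rules disagree in 2 of 8 patterns: one unnecessary escalation and one missed. In two of the six that agree (Yes/No/No and No/Yes/No), the escalation comes only from a Yes that means normal.

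**Reading B: 3a is asked only after Yes to item 3.** That Yes has already triggered the rule, so 3a cannot change the routing and nobody is misrouted.

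**The record, on either reading.** The form does not say how three replies become one. A tick at Yes may stand for normal function or for constant urge. A tick at No may stand for lost sensation of fullness or for the absence of urge.

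**Overlap with other items.** Item 2: "Do you have a new or recent problem in being able to pass urine". Item 3: "Do you have a new or recent loss of control of your bladder and/or your bowels". Item 4: "Do you have numbness or altered feeling or pins/needles around your back passage or genitals". On all three, Yes is the concern. None asks whether the patient can tell when the bladder is full; only 3a does.

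**After the fix.** With three separate answers, either reworded so that Yes is the concern or scored against the triggers No, No, Yes, the rule agrees with the meaning in all 8 patterns (0 misrouted).

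**The case against.** The strongest reply is that 3a is a prompt under item 3. Its number marks it as a sub-item, and the article's count of 12 symptoms fits items 1 to 12 only. It is no answer to say that such a prompt would be pointless because it cannot alter escalation: the same holds for 12a, and a prompt can supply detail for the clinician discussion. This stands. On that reading routing is unaffected. What remains is that 3a, unlike 12a, is not marked as conditional and has its own Yes/No pair, so the stand-alone reading is also open, and the recorded answer is ambiguous on both.

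A second reply is that the consequence is already contained. A person asks the questions by telephone, items 2 to 4 cover neighbouring symptoms in the right direction, and the entry condition and exclusion criterion are worded by meaning. This also largely stands. The remaining gap is that neither the entry condition nor the exclusion criterion provides the discussion with a senior clinician.

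A third reply is that interviewer instructions may exist in the full protocol, which is not shown. They may, but the article prints the questions and the rule, and as printed the two do not fit together.

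**Conclusion.** The point holds as a minor defect in the form. Item 3a mixes directions on one answer, and the rule acts only on Yes. Read as a stand-alone item, 2 of 8 answer patterns are misrouted. Read as a follow-up to item 3, none are, and only the ambiguous record remains. The article does not settle which reading is meant.

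The 2 of 8 assumes that the rule is applied literally to the three replies. It counts patterns, not patients; the article gives no frequencies, the patterns are not equally likely, and the figure does not measure risk.

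A reader might infer that patients with serious bladder symptoms will be enrolled. The documents do not support that: the entry condition and exclusion criterion should keep them out, and items 2 to 4 may identify many of them. A reader might also infer a higher count of misrouted patterns by supposing that the single box records only one of the three parts. Nothing in the article says so, and the stated rule gives 2.

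**What to change.** Record the three parts of 3a separately, in one of two ways:

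- Reword so that Yes is always the concern, for example: any new problem with how the bladder is working; loss of the feeling of when the bladder is full; wanting to go all the time. The escalation rule can then stay as it is.
- Keep the wording, print the trigger answer for each part (No, No, Yes), and change the rule so that it acts when a patient gives the trigger answer.

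If 3a is meant only as a follow-up to item 3, also mark it as conditional in the way 12a is marked.

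The cost is a revised one-page screening form and, under the second option, one reworded sentence. No extra patients or staff are needed.

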### Randomisation and blinding

The internet intervention software will automate the randomisation process for this trial. The randomisation sequence is automatically generated, and a computer-generated algorithm block randomises patients to the trial groups. As the sample size is small, blocking is being used to increase the chance of approximately equal numbers of patients allocated to each group. Patients are stratified by severity (≥7 on the Roland-Morris Disability Questionnaire^31^). As the software randomises patients, the sequencing will be concealed from the trial team. Patients will be automatically informed of their allocated group via the internet through the intervention website. As the intervention is primarily behavioural, patients will not be blind to allocation. Telephone outcome data will be collected by an independent research assistant blind to group allocation. The trial statistician will remain blind to allocation until full analysis is finalised. See figure 1 for patient flow through the trial.

**Figure 1 BMJOPEN2015009524F1:**
[figure not shown]
Diagram showing the flow of patients through the trial (GP, general practitioner; LBP, low back pain).

### Interventions

Details of the interventions (adhering to SPIRIT^32^ and TIDIER^33^ guidelines on reporting) are provided below.

#### Usual care

Patients allocated to this arm will continue to receive usual care from their GP. In the first instance, National Institute for Health and Care Excellence (NICE)^13^ recommended care for LBP consists of education and self-management advice, including advice to stay active. GPs may also make referrals to other health professionals who can offer other recommended treatments such as exercise programmes, manual therapy or acupuncture or to pain management programmes. With regard to pharmacotherapy, recommendations are for paracetamol initially, followed by NSAIDs or weak opioids.^i^ In practice, many GPs do not adhere to guidelines for LBP.^34^ It is likely that treatment received as part of usual care will vary, and this variation will be documented in the present study. If a patient does not reconsult over the study period, they may receive no additional care beyond that which they received as part of their initial GP consultation, whereas some patients may receive ongoing care from the GP, and/or referrals for diagnostic tests or treatments from other healthcare professionals such as physiotherapists or other specialists.

